Moreover, our research shows that the detection of some upper respiratory tract microbes is associated with more prolonged illness and more severe symptoms at days 2 to 4, suggesting that detecting microbes could help manage patient expectations for subsequent illness trajectory and could help identify subgroups more (and less) likely to benefit from antibiotic (antiviral) treatment.

We considered multiplex systems would provide more clinical certainty than single or duplex POCTRMs systems. We are aware of three multiplex POCTRMs manufacturers: bioMérieux (Biofire® Respiratory 2.1), GenMark (ePlex new respiratory pathogen) and Qiagen (QIAstat-Dx Respiratory panel). The bioMérieux

system will be used in the RAPID-TEST trial because of its: high test accuracy, established technology (since 2011), fastest time-to-result (45 minutes compared to 1-2 hours), lowest price per test and because we used the same system in our feasibility study.

There is currently insufficient evidence regarding the safety, efficacy, or mechanism of action, let alone clinical and cost effectiveness, to recommend use of POCTRMs in primary care. Efficacy studies are urgently needed to address these issues using randomised controlled designs, as well as qualitative methods to understand clinician and patients' perceptions of the tests. The RAPID-TEST trial will show whether using multiplex POCTRMs in primary care could safely reduce the unnecessary use of antibiotics, and the beliefs that sustain unnecessary use, thereby reducing the public AMR risk. We will also show whether POCTRM use affects patient outcomes, antiviral prescribing, re-consultations and future consultations for RTIs. Results will inform the design of future pragmatic studies to investigate clinical and cost-effectiveness of POCTRMs in primary care.

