| 5. The proportion with new or worsening symptoms ≤28 days                                                                                                                               | Any new symptoms or worsening of pre-existing symptoms                                                                                                                                                                                                                                                                                                                                                                                                               | Trial Diary  completed daily by participant               |
| 6. The proportion consulting after Appointment Two and ≤28 days for RTI (with/out evidence of it being for the same illness, with/out evidence of the same illness having deteriorated) | Documentation of any RTI related consultation (in and out of normal office hours) after Appointment Two and ≤28 days, whether for the same symptoms /illness as the recruitment consultation with/out documentation that symptoms are getting worse                                                                                                                                                                                                                  | Retrospective collection from PCMR at least 2 months after recruitment |
| 7. The proportion with hospital admissions for respiratory infections ≤28 days                                                                                                          | Evidence of any hospital admission for a respiratory infection in the medical records ≤28 days                                                                                                                                                                                                                                                                                                                                                                       | Retrospective collection from PCMR at least 2 months after recruitment |

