| E Optional
Clinician DCE
Survey                                                                                   | Throughout trial after all the clinician interviews are completed                                                   |                                                                                                    |                                          |                                                |                                     |                                             |                                          |                                                |                                    |                                          |             |             |

AWhere the participant is in the No GP POCTRM test group, this data can be completed immediately after randomisation. Where the participant is in the GP POCTRM test group, the Study Clinician must wait until the POCTRM results are available before completing this data.

BFor participants <16 years on Day 1, their parent/carer will be asked to provide parental views on behalf of their child for the participant views on Day 1, the 2 Month Questionnaire and the optional interview and DCE survey.

CTrial Diary needs to be completed at baseline by the participant (or their parent/carer for participants <16 years) and then daily from Day 1 until their symptoms resolve or up to Day 28, whichever comes first. The EQ-5D will be completed at baseline and then weekly from Day 1 up to the end of the week that symptoms resolve.

DAt 2 months, this will be data collection of GP consultations and hospital admissions for respiratory tract infections and antibiotic or antiviral prescribing up to Day 28. At 6 months, this will be data collection of GP consultations for respiratory tract infections occurring between Day 29 and up to 6 months.

EStudy Clinicians involved in the trial and other clinicians recruited through the West of England Clinical Research Network will be invited to complete a Clinician DCE Survey.

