## 9.2 Identification of AEs

AEs are expected to occur throughout the course of the trial. Site teams are responsible for recording appropriate AEs for their participants during the trial. The central trial team will contact the sites if additional information is required e.g. to ascertain the nature and severity of an AE. If a participant attends a routine i.e. non-trial related appointment, and an AE is reported, the site team will assess and log this according to the trial recording and reporting procedures as detailed below.

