## 9.5 Recording SAEs

Sites will record all SAEs in the SAE Summary Log in the eCRF. Data capture will be via the trial database, or in a suitable electronic format or via paper records with subsequent data entry, where necessary. The central trial team will review the SAE Summary Log regularly for monitoring and reporting purposes and will prepare regular summary reports of all SAEs for discussion at relevant oversight meetings, including with the DMC.

SAEs should also be recorded in the participant's medical notes by the site. The participant should be followed up by the site until the event resolves or a final outcome has been reached. The PI, or delegate, should complete the overall assessment. Information not available at the time must be forwarded once available.

As is proportionate to the nature of the trial, only SUSARs will require expedited reporting to the Sponsor.

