| Number of respiratory infection consultations  | Count       | The number of respiratory infection consultations within 28 days and after 28 days but within 6 months.  |
| Hospital admissions for respiratory infections | Binary      | One or more hospital admissions for a respiratory infection within 28 days, from medical records review. |

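### The 2-month record review takes only respiratory admissions, and no search is described for other serious events, so the by-arm SAE count may be incomplete or uneven

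*Combined protocol and SAP*

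**What the plan says.** **Record review.** Protocol Table 1 (other secondary objective 7) defines the admission outcome as "Evidence of any hospital admission for a respiratory infection in the medical records ≤28 days". Table 5, footnote D, sets the scope of the 2-month review: GP consultations and "hospital admissions for respiratory tract infections and antibiotic or antiviral prescribing up to Day 28". For the later review the same footnote says: "At 6 months, this will be data collection of GP consultations for respiratory tract infections occurring between Day 29 and up to 6 months". SAP 2.10.2 carries the admission outcome forward as "One or more hospital admissions for a respiratory infection within 28 days, from medical records review", and SAP Table 4 has a single hospitalisation row, for RTI.

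**Serious events.** Protocol 9.5 states: "Sites will record all SAEs in the SAE Summary Log in the eCRF". The SAE definition in protocol Table 7 is not limited by cause, and its note on hospitalisation covers unplanned overnight stays after formal admission. On how events come to light, protocol 9.2 makes site teams responsible and describes one route: "If a participant attends a routine i.e. non-trial related appointment, and an AE is reported, the site team will assess and log this". The site PI judges seriousness, expectedness and relatedness (9.3). Participants and Study Clinicians are told the allocation (6.11).

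**Use of the data.** SAP 3.2 and Supplementary Table 7 show, by arm, how many participants had 0, 1, 2 or 3+ SAEs of any kind. Protocol 1.1 says the trial will show whether use of the tests "in primary care could safely reduce the unnecessary use of antibiotics".

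**The concern.** The plan will report two counts of serious outcomes that are found in different ways. Respiratory admissions are looked for in every participant's record. The all-SAE count covers a wider set of harms, but nothing in the visible text sends anyone to look for them.

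The panel does not test for three typical respiratory bacteria (protocol 6.6.1). An untreated bacterial illness that progresses after a virus-positive result is therefore a foreseeable harm for any statement about safe reduction. If the person reading the record does not regard the resulting admission as respiratory, it reaches the trial only through the SAE log. Table 7 also says that signs or symptoms of the respiratory infection, and treatment failure, are not AEs. That may leave a site unsure whether to log a deterioration.

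An incomplete log makes low counts look more reassuring than they are. If completeness differs between arms in an open-label trial, the by-arm table is biased, and the documents do not tell us in which direction.

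**Working it through.** **Step 1. Which planned source would find an any-cause admission or death by Day 28?**

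| Source | What it collects | Lists any-cause admission or death? |
|---|---|---|
| 2-month PCMR review (Table 5, note D) | RTI consultations, RTI admissions, antibiotic and antiviral prescribing to Day 28 | No |
| 6-month PCMR review (Table 5, note D) | RTI consultations after Day 28 | No |
| Trial Diary (Table 5, note C; SAP 2.10.2) | Symptoms, medicines, EQ-5D | No such item described |
| 2-month questionnaire (6.9) | Beliefs and consulting intentions | No |
| Regular contacts from the central team (6.9) | Support for diary completion | No safety enquiry described |
| SAE Summary Log (9.5) | All SAEs | Yes, but no scheduled search feeds it |

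No step compares the PCMR extraction with the log, so even the respiratory admissions in SAP Table 4 and the SAEs in Supplementary Table 7 could disagree.

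**Step 2. Denominator.** The plan gives no figure for safety ascertainment. Its only relevant number is the sample size (protocol 10.1.1): 60% v 45%, 90% power, 5% significance (taken as two-sided).
- Uncorrected: n = [1.96 × √(2 × 0.525 × 0.475) + 1.2816 × √(0.60 × 0.40 + 0.45 × 0.55)]² / 0.15² = 231 per group.
- Continuity-corrected: (n/4) × [1 + √(1 + 4/(n × 0.15))]² = 244, the plan's figure.
- With 5% attrition: 244/0.95, rounded up, = 257 per arm, or 514 in total, as stated.

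**Step 3. Incomplete ascertainment, equal in both arms (illustration).** Let f be the fraction of serious events that is recorded. Neither f nor any event rate is in the documents, so the values below are assumptions shown over a range.
- Upper bound on the true rate if no event is recorded in an arm: (1 − 0.05^(1/257))/f.
- Chance of recording at least one event at a true rate of 1%: 1 − (1 − 0.01f)^257.
- Power for a true 1% v 3% (normal approximation, two-sided 5%, 257 per arm, both rates multiplied by f).

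| f | Upper bound | Chance of ≥1 recorded | Power, 1% v 3% |
|---|---|---|---|
| 1 | 1.2% | 92% | 37% |
| 0.75 | 1.5% | 86% | 29% |
| 0.5 | 2.3% | 72% | 21% |
| 0.25 | 4.6% | 47% | 12% |

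In events: at an assumed 2% rate, 257 × 0.02 = 5.1 per arm. If half are non-respiratory and half of those are missed, 5.14 × 0.5 × 0.5 = 1.3 are lost per arm.

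**Step 4. Unequal ascertainment (illustration).** The observed risk ratio is the true ratio multiplied by f(intervention)/f(control).
- True rate 2% in both arms, f = 0.5 v 0.75: 257 × 0.02 × 0.5 = 2.6 recorded against 257 × 0.02 × 0.75 = 3.9, ratio 0.67. Reversed, the ratio is 1.5.
- True doubling, f = 0.5 v 1.0: 2 × 0.5/1.0 = 1.0, so the doubling disappears.

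**The case against.** Much can be said for the plan as written.

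- **The events are already reportable.** Sites must log every SAE. The central team reviews the log regularly (9.5), SAEs go to the DMC (9.5.1), and delegated monitoring would typically check SAE recording (13.1). The sites are GP practices, so the body that must log also holds the record. This stands: the gap is in how events are found, not in whether they count.
- **The record review is wider than admissions.** There are two reviews. The 2-month one takes RTI consultations in and out of hours, and its prescribing item is not restricted to RTI in wording, so it may hint at some treated complications. This stands, but a prescription is only indirect evidence of an admission.
- **Participants are in contact with the trial.** The central team contacts them about the diary and they are told to approach the practice with concerns (6.9). True, but neither is a safety enquiry.
- **Part of the plan is not visible.** The AE and SAE recording frameworks (protocol Figures 3 and 4) are not shown and the CRFs are not included. An active step could be there, so the point is limited to the visible text.
- **Safety does not rest on this count.** There is a non-inferiority comparison of symptom severity, with worsening symptoms, reconsultation and RTI admission beside it. SAEs are tabulated without a test. On the assumed 1% v 3%, power is only 37% with perfect ascertainment, so the trial could not settle rare harms either way. This stands and lowers the priority.

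A reader might infer that a complication such as sepsis is excluded from SAP Table 4. The documents do not support that: no code list is given, and sepsis arising from a chest infection could be counted under the wording of Table 1.

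**Conclusion.** The point holds as a modest one. The record review does not collect non-respiratory admissions or deaths. The visible text describes no active search for them, and the sites that log them know the allocation. The by-arm count of all SAEs may therefore be incomplete or unevenly ascertained.

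The size cannot be derived from the documents. Every figure in steps 3 and 4 rests on assumed rates and recording fractions. They show only that, with a handful of events per arm, moderate under-recording or a moderate imbalance would matter to how the table reads. A reader might go further and infer that a known number of events will be lost, or that missed cases will decide the safety conclusion. Neither is supported: no rate is given, the SAE table is descriptive, and under-recording is possible rather than shown.

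The primary outcome, the sample size and the key secondary analysis are unaffected. The change is worth making because it is cheap and the trial intends to speak about safe reduction.

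**What to change.** 1. **Collect.** At the existing 2-month PCMR review, on the same form in both arms, record every unplanned overnight admission and every death from randomisation to Day 28, whatever the cause, with date and diagnosis. Test results are filed in the participant's notes (protocol 6.6.1), so extraction blind to allocation may not be feasible. Identical factual fields for everyone are the practical safeguard.
2. **Reconcile.** Compare these entries with the SAE Summary Log before the lock that contains safety reporting. Under protocol 6.11 that is the second lock, whereas the 2-month PCMR data are in the first. If reconciliation is wanted before the TMG sees unblinded results, 6.11 must be amended.
3. **Report.** Add a descriptive row to SAP Table 4 for any-cause unplanned admission or death, beside the respiratory row. Label its window, since it starts at randomisation and the existing row starts at Appointment Two. Supplementary Table 7 gives no window: state one, and base its Day 1–28 SAE counts on the reconciled list.

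**Cost.** A few fields while the record is open, and a second look at records already reviewed if earlier participants are to be included. Willingness to have outcome data taken from the record is already an inclusion criterion (5.2.2); the consent wording should be checked for the added items. Unrelated admissions add noise, but only to the added row. The target stays at 514.

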**Table 2: Qualitative and Discrete Choice Experiment (DCE) Objectives and Outcomes**

| Objective                                                                                                                                                                                                                                                | Outcome Measure                                                                                     | Source and published reference (where applicable) |
|----------------------------------------------------------------------------------------------------------------------------------------------------------------------------------------------------------------------------------------------------------|-----------------------------------------------------------------------------------------------------|---------------------------------------------------|
| 1. To explore participants' (or parents'/carers' if the participant is <16 years) understanding of the test and the result they were given, and their views of the implications for treatment and future consultations                                   | Participant responses to qualitative questions                                                      | Participant interview                             |
| 2. To explore the trade-offs participants (or parents/carers if the participant is <16 years) make in choosing to visit the GP with respiratory infection symptoms and the extent POCT RM s might increase or decrease help seeking behaviour | Discrete choice experiment (DCE) survey to be developed based on qualitative participant interviews | Participant DCE survey                            |
| 3. To describe the situations in which clinicians most and least value the new microbial knowledge, and how it influences clinical reasoning and participant management                                                                                  | Clinician responses to qualitative questions                                                        | Clinician interview                               |
| 4. To explore the trade-offs clinicians make about whether and when to use the POCT RM                                                                                                                                                        | DCE survey to be developed based on qualitative clinician interviews                                | Clinician DCE survey                              |

**Table 3: Mechanistic Objectives and Outcomes**

| Objective                                                                                                                                                                                                                         | Outcome Measure                                   | Source and published reference (where applicable)                                    |
|-----------------------------------------------------------------------------------------------------------------------------------------------------------------------------------------------------------------------------------|---------------------------------------------------|--------------------------------------------------------------------------------------|
| Primary mechanistic objective
To determine whether there are overall (GP POCT RM test vs. No GP POCT RM test) and differential (virus detected vs. not detected) effects with respect to reducing | See Appendix 1 (Study Clinician views question 1) | Study Clinician views at Steps 2 and 5 (Figure 1) and POCT RM result. For |

| Objective                                                                                                                                                                                                                                                                                                                                                                                                                                                                                                                                                                  | Outcome Measure                                                                                                                                                                                          | Source and published reference (where applicable)                                                                                  |
|----------------------------------------------------------------------------------------------------------------------------------------------------------------------------------------------------------------------------------------------------------------------------------------------------------------------------------------------------------------------------------------------------------------------------------------------------------------------------------------------------------------------------------------------------------------------------|----------------------------------------------------------------------------------------------------------------------------------------------------------------------------------------------------------|------------------------------------------------------------------------------------------------------------------------------------|
| the number of participants for whom the Study Clinician believes antibiotics are necessary (as a mediator of the primary clinical outcome)                                                                                                                                                                                                                                                                                                                                                                                                                                 |                                                                                                                                                                                                          | published references see Appendix 1.                                                                                               |
| Secondary mechanistic objective
To describe the effect of POCT RM results on Study Clinician and participant (or parent/carer if the participant is <16 years) beliefs in the necessity, and benefits, of prescribing antibiotics for the respiratory infection, and confidence in the value of the POCT RM to guide the prescribing decision and explore relationships of Study Clinician and participant (or parent/carer if the participant is <16 years) beliefs, attitudes and intentions with antibiotic prescribing and consumption | See Appendix 1 (Study Clinician views questions 2 to 7; and Participant views questions 1 to 5).                                                                                                         | Study Clinician views at Steps 2 and 5, Participant views at Steps 1, 3 and 7 (Figure 1). For published references see Appendix 1. |
| Tertiary mechanistic objectives                                                                                                                                                                                                                                                                                                                                                                                                                                                                                                                                     |                                                                                                                                                                                                          |                                                                                                                                    |
| 1. To investigate the extent to which control group Study Clinician antibiotic prescribing is better than chance with respect to 'virus detected' and 'no virus detected' results                                                                                                                                                                                                                                                                                                                                                                                          | Antibiotic prescribing (including delayed prescribing) for a RTI at Appointment Two (Step 6, Figure 1)
Central research laboratory POCT RM result                                          | Study Clinician/Study Champion completed REDCap data
Central research laboratory results                                        |
| 2. To explore the relationships between baseline symptoms and signs, POCT RM result, antibiotic consumption and participant reported: (i) mean symptom severity at days 2 to 4 A ; (ii) duration of moderately bad (or worse) symptoms                                                                                                                                                                                                                                                                                                               | Baseline symptoms and signs
POCT RM result
Any antibiotic consumption at ≤7 days
Mean symptom severity at Days 2 to 4 A
Duration of moderately bad (or worse) symptoms | Baseline CRF
POCT RM result
Trial Diary  completed daily by participant                              |
| 3. To assess agreement between POCT RM results at GP practices vs. POCT RM results at the central research laboratory (intervention group only)                                                                                                                                                                                                                                                                                                                                                                                                      | POCT RM results at GP practices vs. POCT RM results at central research laboratory                                                                                                 | POCT RM results from GP practice and from central research laboratory                                                   |
| 4. To assess agreement between POCT RM results at central research laboratory vs. extended laboratory respiratory virus and bacteria testing                                                                                                                                                                                                                                                                                                                                                                                                                    | POCT RM results at central research laboratory vs. extended laboratory testing                                                                                                                | Central research laboratory results                                                                                                |
| 5. To assess the relationship between weekly EQ-5D measures and symptom severity scores                                                                                                                                                                                                                                                                                                                                                                                                                                                                                    | EQ-5D-5L or EQ-5D-Y and mean daily symptom severity                                                                                                                                                      | EQ-5D-5L  (EQ-5D-Y for children aged ≥4 to <16 years) completed weekly                                                |

| Objective | Outcome Measure | Source and published reference (where applicable)            |
|-----------|-----------------|--------------------------------------------------------------|
|           |                 | and Trial Diary  completed daily by participant |

A Day 1 is the day of randomisation

